#### Randomization and blinding

2.3.2

Randomization is standardized in this study in combination with the design characteristics of the three parts of the experiment: The first part is a case–control observational study. After screening through strict inclusion and exclusion criteria, the case group (patients with lumbar muscle strain) and the control group (healthy people without lumbocrural pain) are selected from the eligible population by simple random sampling (15 cases in each group) to ensure sample representativeness, with no inter-group random allocation involved. The second part is a cross-over design study, in which 24 patients with lumbar muscle strain are divided into 3 groups (8 cases in each group) by complete randomization, receiving three sequences of rolling manipulation intervention with low-medium-high, medium-high-low and high-low-medium pressure, respectively. The third part is an interventional trial involving 69 participants in total. 46 patients with lumbar muscle strain are stratified by age and disease duration and then divided into a case intervention group (rolling manipulation intervention, *n* = 23) and a case control group (health education intervention, *n* = 23) by the random number table method; additionally, 23 healthy controls are selected by simple random sampling.

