Oswestry Disability Index (ODI) (Part 3): The primary clinical outcome is the Oswestry Disability Index (ODI). The main analysis will compare the change in ODI from baseline to immediately after the 6th intervention between the case intervention group and the case control group. We expect a greater reduction in ODI in the case intervention group. ODI will also be assessed after the 1st and 3rd interventions to describe the course of clinical change. It covered 10 dimensions including pain intensity, activities of daily living, walking, sitting and sleeping, with 0–5 points for each dimension. The total score is converted into a percentage (0–100%), with a higher score indicating more severe dysfunction. Data are collected before intervention and immediately after the 1st, 3rd and 6th interventions to evaluate improvements in patients’lumbar function. If no more than 1 item is missing, the value is replaced by the average score of the completed items; if 2 or more items are missing, the data are regarded as invalid.

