### Sample size calculation

2.8

Based on the core research objectives and design types of the three parts, this study is overall planned as follows:

The first part is an observational study, with the fNIRS-derived cortical hemodynamic response (HbO/HbR changes) as the primary outcome. Based on repeated measures analysis of variance (effect size *f* = 0.286, α = 0.05, 1−β = 0.8) (30), G*Power 3.1.9.7 calculation showed that 12 cases are needed in each group. Considering a 20% attrition rate, 15 cases are included in both the healthy control group without lumbocrural pain and the lumbar muscle strain case group, with a total of 30 cases.

The second part is a cross-over design. The sample size was estimated based on the median frequency (MF) of the surface electromyographic (sEMG) signals, one of the primary electromyographic outcomes for screening the optimal pressure. Referring to our previous study on rolling manipulation in patients with lumbar muscle strain (13), the within-individual standard deviation of sEMG frequency was 17.09 Hz and the intraclass correlation coefficient was 0.5. Repeated Measures ANOVA combined with Greenhouse–Geisser corrected F test (α = 0.05, 1-β = 0.8) was adopted. PASS 2021 software calculation showed that 17 cases are needed. Considering a 20% attrition rate, 24 patients with lumbar muscle strain are included and randomly divided into 3 group sequences.

The third part took the change in the Oswestry Disability Index (ODI) from baseline to immediately after the 6th intervention as the primary clinical endpoint for the comparison between the case intervention group and the case control group. Based on a two-independent-sample design, in which the expected between-group difference (μ2 − μ1 = 10) and the standard deviation (σ = 9) were derived from a previous study on massage combined with functional exercise for chronic lumbar muscle strain (31), With α = 0.05 and 1 − β = 0.80, the calculation showed that 18 patients were required in each group. Considering a 20% attrition rate, 23 patients with LMS will be enrolled in the case intervention group and 23 in the case control group, resulting in a total of 46 patients with LMS. In addition, 23 healthy controls will be enrolled as a reference group for the fNIRS and biomechanical comparisons. Therefore, Part 3 will include 69 participants in total, comprising 46 patients with LMS and 23 healthy controls.

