### Statistical analysis

2.10

Statistical analyses will be performed using MATLAB R2024b. fNIRS preprocessing and calculation of HbO/HbR concentrations, functional connectivity (FC), wavelet amplitude (WA), and graph-theoretical measures will be performed using NirSpark V1.8.9. Normally distributed continuous variables will be expressed as mean ± standard deviation, non-normally distributed variables as median and interquartile range, and categorical variables as frequencies and percentages. Normality will be assessed using the Shapiro–Wilk test. *p* < 0.05 will be considered statistically significant.

Baseline data: Baseline variables will be analyzed according to variable type, data distribution, and the number of groups using the t test, analysis of variance (ANOVA), Mann–Whitney U test, Kruskal-Wallis test, or chi-square test, as appropriate.

fNIRS data: Task-related fNIRS data will be analyzed using the general linear model (GLM) implemented in NirSpark to obtain channel-wise HbO and HbR β coefficients for subsequent group comparisons. To reduce the risk of false-positive findings arising from multiple comparisons, statistical tests of channel-wise activation will be corrected using the false discovery rate (FDR). Functional connectivity (FC), wavelet amplitude (WA), and graph-theoretical measures calculated in NirSpark will be exported for subsequent statistical analysis using linear mixed-effects models (LMM), with Bonferroni correction applied to multiple comparisons.

Biomechanical and clinical data: Repeatedly measured sEMG, muscle tension, pressure pain threshold (PPT), VAS, and ODI outcomes will be analyzed using repeated-measures ANOVA when the data are normally distributed. For non-normally distributed repeated measurements, generalized estimating equations (GEE) will be used in Parts 1 and 3, whereas the Friedman test will be used for the low-pressure, medium-pressure, and high-pressure conditions in Part 2. Bonferroni correction will be applied where multiple comparisons are required.

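### Part 3 stratifies its randomisation by age and disease duration, but the stated ODI analysis does not include those two factors

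*Protocol article*

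**What the plan says.** Protocol article, 2.3.2 (Randomization and blinding): for Part 3, "46 patients with lumbar muscle strain are stratified by age and disease duration and then divided into a case intervention group" and a health-education control group, 23 in each, "by the random number table method". Cut-points for age and duration, and the number of strata, are not given.

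Section 2.5.2 (Primary outcome measures) fixes the primary comparison: "The main analysis will compare the change in ODI from baseline to immediately after the 6th intervention", intervention against control.

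Section 2.10 (Statistical analysis) names the method: "VAS, and ODI outcomes will be analyzed using repeated-measures ANOVA when the data are normally distributed". Otherwise "generalized estimating equations (GEE) will be used in Parts 1 and 3". No stratification factor or other covariate is mentioned for either route.

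Section 2.8 (Sample size calculation) treats the comparison as two independent samples with a difference of 10 and an SD of 9, without strata: "With α = 0.05 and 1 − β = 0.80, the calculation showed that 18 patients were required in each group". After attrition, "23 patients with LMS will be enrolled in the case intervention group and 23 in the case control group".

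**The concern.** Stratifying by a factor makes sense if the factor is expected to predict the outcome. If it does, and the arms are balanced on it, the difference between arms varies less from trial to trial than it would under simple randomisation. An analysis that ignores the factor leaves its contribution in the error term. The reported standard error then overstates the real uncertainty, the confidence interval is too wide and the p-value too large.

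If the arms are not balanced within strata, the unadjusted standard error is correct for that design, but the analysis still gives up the precision that adjustment would bring.

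At stake is efficiency and calibration in a 46-patient comparison, not protection against false positives. The eligible range is wide (age 18–69, pain for more than 3 months with no upper limit, section 2.2.1), so it is plausible, though not shown, that these factors matter for ODI change.

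**Working it through.** **Inputs from the article.** Difference 10, SD 9, α = 0.05, power 0.80, 18 evaluable and 23 enrolled per group (2.8). Stratification by age and duration (2.3.2). ODI model without these factors (2.10).

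**Assumptions.** Two-sided test. SD 9 is the SD of ODI change. R², the share of its variance explained by the strata, is 0.1 or 0.2. For the simulation there are four strata of 12, 12, 11 and 11 (two levels per factor).

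**1. The plan's own figure.** n per group = 2(z₁₋α/₂ + z₁₋β)²σ²/δ².
- Power 0.80: 2 × (1.960 + 0.842)² × 81/100 = 12.7, so 13 (14 by the exact t calculation).
- Power 0.90: 2 × (1.960 + 1.282)² × 81/100 = 17.02, so 18 (19 by t).

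The stated 18 is not reproduced at 80% power; it fits 90%. The step from 18 to 23 is reproduced: 18/0.8 = 22.5, so 23. This point does not depend on the mismatch, which lies on the generous side.

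**2. Standard error at 23 per group.** Without strata, SE = σ√(2/n) = 9 × √(2/23) = 2.65. With strata in the model, SE = 2.654 × √(1 − R²).

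| R² (assumed) | SE without strata | SE with strata | Cut in SE | 95% CI half-width, without → with |
|---|---|---|---|---|
| 0.1 | 2.65 | 2.52 | 5% | 5.35 → 5.08 |
| 0.2 | 2.65 | 2.37 | 11% | 5.35 → 4.79 |

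**3. Type I error of the unadjusted test when allocation is balanced within strata.** The true SE is √(1 − R²) times the reported one, so the test rejects only when a correctly scaled t exceeds the critical value divided by √(1 − R²). With 44 degrees of freedom the critical value is 2.015.
- R² = 0.1: 2.015/0.949 = 2.124, two-sided tail about 3.9%.
- R² = 0.2: 2.015/0.894 = 2.253, two-sided tail about 2.9%.

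Simulation with blocks of 4 within the four assumed strata (20,000 runs) gave 4.0% and 3.0%. With the strata in the model it gave 5.2% and 5.3%, close to the nominal 5%.

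**4. Type I error when allocation is not balanced within strata.** Simulated simple allocation gave 5.1% and 5.2% for the unadjusted test. It is valid; only the gain in step 2 is missed.

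**5. Power.** For a difference of 10 at 18 per group: 90% without strata, against 93% (R² = 0.1) and 95% (R² = 0.2) with them. If the true difference were 7 (an illustrative value, all 46 patients, blocks of 4): 74% against 77%, and 76% against 82%.

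**The case against.** **Covariate lists are often left to the full protocol or analysis plan.** That is fair, and section 2.10 does not exclude covariates. But the article does more than stay silent: it names the stratification factors and it names the ODI model, and the two do not match. This supports a request to align them, not a charge of error.

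**The size is hypothetical.** Nothing in the article links age or duration to ODI change, so the 10% to 20% is assumed. With no link, adjustment gains nothing and costs a few degrees of freedom. On the article's own inputs, power is about 90% at 18 per group without adjustment, and any miscalibration is conservative. All of this stands and keeps the point minor.

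**A stronger reading is that the stratification fails to secure balance**, because a random number table means unrestricted allocation within strata. The article does not support this. A table is a source of random order and can be used with blocks or with equal halves per stratum. The fixed 23/23 split points to some restriction, since unrestricted allocation gives it with probability C(46,23)/2⁴⁶ = 0.12. Under the four assumed strata, the chance that some stratum differs by 4 or more between arms is 78% if unrestricted, 61% if only the total is fixed, and 0% with blocks of 4 or equal halves. The article does not say which applies, and such detail commonly sits in the full protocol.

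**A reader might also infer that the stratification adds no precision.** That goes too far. Balance on prognostic factors lowers the true variance of the difference even if the model ignores them. What is lost is the use of that gain in the reported SE and p-value.

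**Conclusion.** The point holds as a minor improvement. The ODI analysis in 2.10 omits the factors by which 2.3.2 stratifies the randomisation. If those factors explain 10% to 20% of the variance in ODI change, including them cuts the standard error by about 5% to 11%. If allocation is also balanced within strata, it moves a conservative test back to its nominal 5%. Without that balance, the unadjusted test is valid and only the precision is lost.

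The figures rest on the assumed variance share, on SD 9 applying to ODI change and, for the simulated error rates, on four strata. None of this makes the planned analysis anti-conservative or the trial underpowered on its own inputs. The article gives no ground for saying that the random number table is misused or must be replaced.

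**What to change.** In 2.10, state that the primary between-group comparison of ODI change to after the 6th intervention includes the age and disease-duration stratification factors, under both the repeated-measures ANOVA and the GEE route.

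The terms have to act on change. In a model of the change score they enter as main effects. In a repeated-measures model of all ODI visits they need to interact with time, because a main effect of stratum alone leaves the group-by-time comparison untouched.

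The cost is one sentence and a few degrees of freedom (three with four strata: 41 instead of 44 for the error term at 46 patients). No patients, visits or measurements are added. The terms should be fixed before outcome data are seen, so that they are not chosen after the baseline comparisons that 2.10 also plans.

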### Interventional measures

2.4

#### Part 1: cortical hemodynamic responses to pain stimulation

2.4.1

First, a rapid muscle condition determinator is used to measure the muscle tension of the left and right lumbar erector spinae and quadratus lumborum of the patients. Then, pressure pain threshold detection is performed using a simulated dynamometer, and the pain degree is divided into a pain-free range (with a touch feeling, VAS 0–3 points) and a high pain threshold (painful but tolerable, VAS 7–10 points). After the pressure pain threshold measurement, the subjects are pressurized according to the obtained values, and functional near-infrared spectroscopy (fNIRS) is used for detection while pressurization is applied: baseline measurement with 6 min of rest before pain intervention; during pain intervention, 30s of pain-free range - 30s of recovery, for 5 cycles; 30s of high pain threshold - 30s of recovery, for 5 cycles; a 6-min resting measurement is conducted after all interventions, and data are collected.

Muscle tension detection points (selected according to the body surface projection of muscles): bilateral erector spinae: marked points at the muscle belly eminence 3 cm beside the 4th lumbar spinous process.

Bilateral quadratus lumborum: marked points at the muscle belly eminence 3 cm beside the 3rd lumbar spinous process at the level between the posterior iliac crest and the 12th rib.

Bilateral pressure pain threshold detection points: marked points at the muscle belly eminence 3 cm beside the 4th lumbar spinous process.

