#### Primary outcome measures

2.5.2

Functional near-infrared spectroscopy (fNIRS) detection (Part 1): The primary outcome is the cortical hemodynamic response measured by fNIRS, expressed as changes in oxygenated hemoglobin (HbO) and deoxygenated hemoglobin (HbR). Measurements are obtained during the pain-free and high-pain stimulation conditions and compared with the pre-stimulation baseline. The primary comparison is between patients with LMS and healthy controls under the two stimulation conditions. We hypothesize that the cortical hemodynamic responses to pressure stimulation differ between the two groups. The fNIRS system used is a portable 49-channel system manufactured by HuiChuang (Danyang, China), consisting of 20 light sources and 16 detectors. The system uses two wavelengths of 730 and 850 nm, with a sampling rate of 11 Hz and a fixed source-detector separation of 3 cm. The probe array was positioned according to the international 10–10 system, with the D8 optode of the array aligned to the Cz position. Optode positions are recorded for each participant using a three-dimensional digitizing system and registered to Montreal Neurological Institute (MNI) space. The 49 channels cover eight predefined cortical regions: the left and right prefrontal cortex (LPFC and RPFC), left and right supplementary motor area (LSMA and RSMA), left and right primary motor cortex (LSM1 and RSM1), and left and right somatosensory association cortex (LSAC and RSAC) (Figure 2), and recorded data from participants in the static prone position and under different pain stimulations (pain-free range, VAS = 0–3; high pain threshold range, VAS = 7–10). Data preprocessing was performed using Nirspark V1.8.9 software. The preprocessing procedure included channel quality assessment, motion artifact identification and correction, band-pass filtering, conversion of optical density signals to hemoglobin concentration, and baseline correction. Channels with poor signal quality were identified according to the software-based quality control procedure and excluded from further analysis. Motion artifacts were automatically detected and corrected using the built-in motion correction algorithm, with a standard deviation threshold of 6 and amplitude threshold of 0.5. A band-pass filter (0.01–0.1 Hz) was applied to remove physiological noise and low-frequency drift. The modified Beer–Lambert law was used to calculate HbO and HbR concentrations with a differential pathlength factor (DPF) of 6. For the pain-stimulation task in Part 1, task-related hemodynamic responses are analyzed using the general linear model (GLM) implemented in NirSpark. The stimulus function is modeled using the built-in hemodynamic response function (HRF), which is defined in the software by two gamma functions separated by 2 s. The resulting β coefficients of HbO and HbR are used for subsequent analysis. For resting-state and continuous rolling-manipulation data, HbO time series are analyzed using functional connectivity, wavelet amplitude, and graph-theoretical measures. In Part 3, these analyses are used to characterize cortical hemodynamic changes before, during, and after optimal-pressure rolling manipulation.

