#### Secondary outcome measures

2.5.3

Muscle tension detection at marked points of bilateral lumbar erector spinae and quadratus lumborum (Part 1,2,3): A rapid muscle condition measurement system (OE-220, ITO, Japan) is used. The detection positions are the bilateral erector spinae (muscle belly eminence 3 cm beside the 4th lumbar spinous process) and bilateral quadratus lumborum (3 cm beside the 3rd lumbar spinous process at the level between the posterior iliac crest and the 12th rib). The probe is pressed vertically on the marked points until a “beep” is heard, then the reading is taken, repeated 3 times (30s interval) to take the average value, and detected at each time node of pain stimulation intervention, rolling manipulation intervention with different pressure and rolling manipulation intervention with optimal pressure.

Pressure pain threshold detection at marked points of bilateral lumbar regions (Part 1,2,3): A simulated dynamometer (NK-500, ALGOL, Japan) is used, with the detection point at the muscle belly eminence 3 cm beside the 4th lumbar spinous process. The test head is pressurized at a constant rate and supervised by VAS score. When the subject reaches the corresponding pain threshold, he/she reported a pause and the data is recorded, repeated 3 times (30s interval) to take the average value, and detected synchronously with each stage of intervention throughout the process.

Visual Analogue Scale for Pain (VAS) (Part 1,2,3): The pain degree is evaluated by a 10-scale sliding ruler. 0–3 points is the pain-free range/low pressure range, 4–6 points is the moderate intensity pain/medium pressure range, and 7–10 points is the high pain threshold/high pressure range. It is used to supervise the intensity of pain stimulation, define the pressure of rolling manipulation and evaluate the pain relief effect after each stage of intervention, and recorded in real time at each intervention node.

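### In Part 1 the resting fNIRS baseline is recorded after painful threshold testing with no recovery interval tied to that step, so the resting-state contrasts may carry after-effects of calibration

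*Protocol article*

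**What the plan says.** Section 2.4.1 sets out Part 1 in order. Muscle tension is measured first. Pressure pain threshold testing follows and establishes two pressures, one in the pain-free range and one at "a high pain threshold (painful but tolerable, VAS 7–10 points"). The fNIRS session comes next: "After the pressure pain threshold measurement, the subjects are pressurized according to the obtained values". Its first element is a "baseline measurement with 6 min of rest before pain intervention". Five pain-free cycles and five high-pain cycles follow, each of 30 s stimulation and 30 s recovery. At the end, "a 6-min resting measurement is conducted after all interventions, and data are collected".

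The testing is done on both sides: "Bilateral pressure pain threshold detection points: marked points at the muscle belly eminence 3 cm beside the 4th lumbar spinous process". Section 2.5.3, which covers all three parts, describes how each reading is taken: "When the subject reaches the corresponding pain threshold, he/she reported a pause and the data is recorded, repeated 3 times (30s interval").

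Section 2.5.2 gives the baseline its role. The primary HbO/HbR responses are "compared with the pre-stimulation baseline". The task data are analysed by a GLM, and resting-state data by connectivity, wavelet and graph measures.

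The text after Table 2 (end of section 2.4.3) asks participants in all three parts to rest quietly for at least an hour before each measurement. The stated reason is to limit the acute effect of physical activity on baseline values.

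**The concern.** A resting recording labelled as preceding stimulation should be free of the stimulus under study. Here each participant has already been pressed on the lumbar muscles up to the pain level that the experiment later applies. A pair of rests around the blocks is informative only if pressing can leave a trace in the resting signal. If it can, the calibration presses may leave one in the first rest.

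Two resting contrasts are exposed. The comparison of the rests before and after stimulation would set one recording that follows painful pressing against another. The comparison of patients with controls would be distorted if the two groups recover from calibration differently. The Discussion invokes central sensitization in chronic musculoskeletal pain, so a difference in recovery is plausible on the protocol's own premise. Giving both groups the same calibration would then not cancel the effect.

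**Working it through.** The protocol states no figure that depends on this point. The check is a reading of the sequence and a count of exposures.

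**1. Order of steps (section 2.4.1).** Muscle tension → threshold testing on both sides, to VAS 0–3 and VAS 7–10 → fNIRS rest, 6 min → pain-free cycles → high-pain cycles → fNIRS rest, 6 min. The baseline follows the painful testing.

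**2. Length of the fNIRS session.** Each set of cycles lasts 5 × (30 s + 30 s) = 300 s = 5 min. The total is 6 + 5 + 5 + 6 = 22 min. Threshold testing lies outside this session, before it.

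**3. Presses before the baseline.**
- Sides: 2 (section 2.4.1).
- Repeats: 3, at 30-s intervals (section 2.5.3).
- Presses per level: 2 × 3 = 6.

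Six presses at VAS 7–10 assumes that the general repeat rule of section 2.5.3 applies to the high level on each side in Part 1. The explicit rule of three repeats for each pressure level appears only in the Part 2 procedure (section 2.4.2). If the pain-free level is also pressed separately, the total is 2 × 6 = 12, of which 6 are painful.

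**4. Comparison with the task.** The task has 5 high-pain blocks of 30 s, or 150 s of held pressure. Section 2.5.3 describes a calibration press as a ramp that stops once the participant reports the target level, and gives no duration. Six presses and five blocks are close in number, but nothing allows them to be compared as doses.

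**5. Gap between the last painful press and the baseline.** No interval is given for this step. The one-hour rest can be read in two ways:
- As a rest before the session, it leaves a gap that could be near 0 min.
- As a rest before every single measurement, it leaves a gap of at least 60 min.

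The second reading would also require an hour between muscle tension and threshold testing, and it conflicts with the measurements in Parts 2 and 3 that are to be taken immediately after an intervention. The first reading is more coherent, but the text does not settle it.

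**6. Which analyses depend on the first rest.**
- Resting connectivity, wavelet and graph measures in Part 1: directly, because that rest is their data.
- Task GLM coefficients: weakly. They are estimated from a block design in which the 30-s recoveries supply the local contrast. The wording in section 2.5.2 that ties the primary outcome to the baseline leaves some dependence.

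**The case against.** The strongest reply is that no harm is shown. The interval is undocumented, the one-hour rest may cover it, and an article commonly leaves session timing to the full protocol. The documents contain no data on how long an after-effect of pressing lasts. Thresholds must be known before individualised stimulation, and a rest after calibration gives a baseline close to the task. The primary comparison is between patients and controls under the two stimulation conditions, estimated by GLM coefficients that depend little on the first rest. No Part 1 hypothesis or named endpoint is a resting contrast. Section 2.5.2 describes the resting-state methods in general terms and then names only Part 3.

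Much of this stands. A reader might infer that the baseline is known to be in a post-pain state, that it falls within minutes of calibration, that the contrast between the two rests necessarily understates the effect of pain, or that the primary outcome is compromised. The documents support none of these. The gap is unstated, the after-effect is unmeasured, its direction is unknown, and the task coefficients are largely protected.

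The order itself still stands, because the article states it explicitly. Thresholds are needed before the blocks, but not before the resting recording. The hour of rest is justified by physical activity and is not placed between the two steps. Even if it did apply there, the baseline would still follow painful testing.

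**Conclusion.** The point holds as a possible bias in the Part 1 resting-state measures. The recording called the pre-stimulation baseline follows threshold testing to VAS 7–10 in all 30 planned participants, and no recovery interval is clearly tied to that testing. It cannot serve as a pain-naive reference. Resting contrasts before versus after stimulation, and between patients and controls, may carry calibration after-effects that could differ between groups.

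The size cannot be given. What can be stated is the exposure, about six painful presses under the assumption on repeats, and a gap from about 0 to 60 min or more depending on how the one-hour rest is read. The primary task coefficients are much less affected. This is a worthwhile and cheap improvement to the measurement order, not a flaw that invalidates Part 1.

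**What to change.** Reorder section 2.4.1:

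1. Record the 6-min resting fNIRS before threshold testing, and name this recording as the baseline for the Part 1 resting-state analyses.
2. Measure the thresholds.
3. Take a short rest as the local baseline for the task.
4. Run the pain-free and high-pain blocks, then the closing 6-min rest, as now.

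Align section 2.5.2 by saying which rest serves as the reference for which analysis, and state whether the one-hour rest applies once per session or between steps. If the present order is kept, give the interval between threshold testing and the resting recording, and limit the interpretation of the resting contrasts accordingly.

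No equipment, visit or participant is added. The cost is somewhat longer cap wear, through bilateral calibration and the short second rest.
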